### 2.10. Statistical Analyses

Statistical analyses will be conducted by an independent statistician from Xiyuan Hospital. In the FAS, patients will be dosed with the study drugs at least one time and one clinical observation will be recorded. Participants with good compliance and without any protocol deviations will be included in the per-protocol set (PPS). Subjects with safety data who have completed at least one study visit will be included in the safety analysis. The mean ± SD will be used in continuous variables. The characteristic comparability between the two groups will be evaluated by a two-sample Student *t*-test for continuous variables and the Fisher exact test or *χ*^2^ test for categorical variables. In this multicenter trial, the Cochran-Mantel-Haenszel test and the analysis of variance will be used. For diminishing the influence of confounding factors on the curative effect, analysis of covariance and the logistic regression model will be applied. For all the analyses, the difference with a value of *P* < 0.05 will be statistically significant. All analyses will be conducted using the SAS software version 9.3 (SAS Institute, Cary, NC, USA).

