## 2. Methods/Design

### 2.1. Study Design

This study is registered with the Chinese Clinical Trial Registry (registration number ChiCTR-TRC-14004639). The multicenter, randomized, double-blind, parallel-controlled, phase IV clinical study follows the recommendations of the CONSORT [8] and SPIRIT statements [9]. This study is financially supported by Jilin Jian Yisheng Pharmaceutical Co. Ltd., Jilin, China. The company is not involved in the clinical trial design, data collection and analysis, or other parts of the study.

Participants will be recruited from three participating centers, namely, Xiyuan Hospital of China Academy of Chinese Medical Sciences, Guan'anmen Hospital of China Academy of Chinese Medical Sciences, and the Second Affiliated Hospital of Tianjin University of TCM. The leading unit among the three centers is Xiyuan Hospital. In this trial, 200 patients will be recruited and randomly allocated to two groups (treatment group, *n* = 100; control group, *n* = 100). Clinical assessment will be performed at baseline (T0, 2 weeks preceding the treatment) and at the end of the 2-week run-in period (T1). Participants will then receive the treatment for 12 weeks. In the treatment period, the intervention assessments are performed at weeks 4 (T2), 8 (T3), and 12 (T4).  Figure 1 shows the study procedures.

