### 2.4. Outcomes and Measures

The primary indicators, HbA1c, fasting blood glucose (FBG), 2-hour postprandial blood glucose (2hPBG), and triglyceride (TG) levels, will be tested at T0, T1, T2, T3, and T4. The secondary indicators, ultrasonic cardiography (UCG) finding, coagulation indicator, and P- selectin level, will be assessed at T1 and T4. Cardiac death, nonfatal myocardial infarction, coronary revascularization, Seattle Angina Questionnaire (SAQ) score, and TCM symptom indicators will also be monitored periodically. Adverse events, which include hemorrhage, will be followed up using electrocardiography, routine urinalysis, routine stool test, and liver and kidney function tests (ALT, AST, Cr, and BUN) from T1 to T4. Items to be measured and the time window of data collection are shown in Table 1.

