### 2.9. Sample Size Calculation

The sample size was determined with a type I error rate of *α* = 0.05 and a power of 80% (type II error rate of *β* = 0.2). According to a previous study, the efficacy rate of Zhenyuan capsules is 94% for relieving angina pectoris symptoms and 64% for placebo [10]. The sample size should therefore consist of 25 participants in each group. Considering the potential 20% loss and the cases that can be counted in each center, 100 participants are needed for each group. As treatment and control groups, and three centers are involved, 200 participants will be recruited in this study. The formula used to calculate the sample size is as follows:(1)$$\begin{array}{c} n=\frac{p_{1}\left(1-p_{1}\right)+p_{2}\left(1-p_{2}\right)}{{\left(p_{1}-p_{2}\right)}^{2}}{\left(\;u_{1-\alpha }+u_{1-\beta }\;\right)}^{2}, \end{array}$$*n* ≈ 25 patients/group.

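### Four unranked primary indicators are each judged at P < 0.05 with no joint success rule, so the chance of at least one false positive primary result is about 9% to 18.5% at a single time point

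*Protocol article*

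**What the plan says.** The Abstract and section 2.4 (Outcomes and Measures) list the same four primary indicators and put none ahead of the others. Section 2.4 reads "The primary indicators, HbA1c, fasting blood glucose (FBG), 2-hour postprandial blood glucose (2hPBG), and triglyceride (TG) levels, will be tested at T0, T1, T2, T3,"; the list of visits ends with T4. Section 2.1 identifies the on-treatment visits: "In the treatment period, the intervention assessments are performed at weeks 4 (T2), 8 (T3), and 12 (T4").

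Section 2.10 (Statistical Analyses) names analysis of variance, the Cochran-Mantel-Haenszel test, analysis of covariance and logistic regression. Its decision rule is: "For all the analyses, the difference with a value of *P* < 0.05 will be statistically significant". It gives no test order, no division of alpha, no primary time point, and no rule on how many of the four indicators must succeed.

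The only other mention of alpha is in section 2.9: "The sample size was determined with a type I error rate of" 0.05. That calculation concerns a different outcome, since "the efficacy rate of Zhenyuan capsules is 94% for relieving angina pectoris symptoms and 64% for placebo [10"].

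**The concern.** Section 2.10 fixes a decision rule, and the rule covers every analysis. Applied to four primary indicators, it gives the trial four separate opportunities to declare a significant primary effect, each at the full 0.05. Three of the four are measures of glucose. A single nominal P value below 0.05 on any of them, with nothing on the other three, would qualify as a positive primary result under the rule as written.

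The Discussion presents this as the first double-blind, parallel-controlled trial of the capsule in this condition and expects robust evidence from it. A primary claim with an unstated and inflated false positive rate would not support that. The defect also cannot be credibly repaired after unblinding, because the choice of success rule could then be guided by the results.

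**Working it through.** **Inputs from the article.** Four primary indicators (Abstract, section 2.4). Threshold 0.05 for each (section 2.10). Three on-treatment visits, T2, T3 and T4 (section 2.1, Table 1). 100 patients per group (sections 2.1 and 2.9).

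**Assumptions.** The article gives no correlations, so a range is shown, with one common value for every pair of indicators. Tests are taken as two-sided.

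**The plan's own figure.** The article states no family-wise error rate, so there is none to reproduce. The sample size can be checked, and it bears on sidedness:

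- [0.94 × 0.06 + 0.64 × 0.36] / 0.30² = 0.2868 / 0.09 = 3.187.
- With the two-sided quantile: 3.187 × (1.960 + 0.842)² = 25.01, which matches the stated 25.
- With the one-sided quantile, as the formula is printed: 19.7.

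The stated 25 therefore implies two-sided 0.05. The calculation concerns angina relief and does not depend on the present point.

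**Step 1: four tests at one time point, independent.** 1 − 0.95⁴ = 1 − 0.8145 = 0.185.

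**Step 2: four tests at one time point, correlated.** Multivariate normal simulation, 400,000 draws, no effect on any indicator:

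| Assumed pairwise correlation | Chance of at least one P < 0.05 |
|---|---|
| 0 | 18.5% |
| 0.3 | 17.4% |
| 0.5 | 15.6% |
| 0.7 | 12.9% |
| 0.9 | 9.3% |

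Even at 0.9 the chance is nearly twice 5%.

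**Step 3: upper scenario, four indicators at three visits.** This applies only if groups are compared at each visit.

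- Independent: 1 − 0.95¹² = 1 − 0.540 = 0.460.
- Correlation 0.5 between indicators and 0.7 between visits: 31%.
- Both correlations 0.9: 15%.

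**Step 4: effect of a correction.** At 0.0125 per test with four independent tests: 1 − 0.9875⁴ = 0.049.

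**Step 5: cost of the stricter threshold.** The standardized difference detectable with 80% power is (z₁₋α/₂ + 0.842) × √(2/n).

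- n = 100 per group: 0.40 at 0.05, and 0.47 at 0.0125.
- n = 80 per group (100 less the 20% loss in section 2.9): 0.44 and 0.53.

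**The case against.** **Two stronger readings do not hold.** First, a reader might infer that twelve tests are planned, because section 2.4 says the indicators are tested at each visit. In context this means laboratory measurement: the list includes T0 and T1, which precede treatment, and Table 1 is a data-collection schedule. Section 2.10 does not say that groups are compared at each visit. The 15% to 46% range is therefore an upper scenario left open by the missing time point, not a description of the plan. Second, a reader might infer that the plan contradicts a trial-wise error rate of 5% that it claims for itself. It claims none. The 0.05 in section 2.9 is a design input for one angina-relief comparison, and angina relief is not a primary indicator.

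**The article is condensed.** A statistical analysis plan may exist and may name a time point and a procedure. This has force for the time point, whose absence alone would not be a finding. It has less force for the threshold, because the article does not stay silent: it states a rule for all analyses. That sentence could be squared with comparing adjusted P values to 0.05, but no adjustment is mentioned anywhere.

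**Joint success might be intended.** Inclusion requires both triglycerides and HbA1c to lie in a given range (section 2.2.1), and the stated aim covers glucose and lipid metabolism together. If all four indicators had to be significant, there would be no inflation. However, no such rule is written, and eligibility criteria do not define trial success. What stands is that joint success is a legitimate option and belongs among the remedies.

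**Correlation reduces the inflation.** This is true, and it is why the range runs down to 9.3%. It does not bring the figure near 5% at any correlation examined.

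**Conclusion.** The concern holds for the four indicators at a single time point. As written, any one of them can be declared a significant primary result at 0.05. The chance of at least one false positive is 18.5% under independence and about 9% to 17% for assumed pairwise correlations of 0.9 down to 0.3. This rests on three assumptions: no effect on any indicator, two-sided tests, and success on any one indicator being enough, which the text permits. Testing each visit as well would raise the figure, but the article does not commit to that, so the conclusion does not depend on it. The point concerns the primary claim and should be settled before unblinding.

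**What to change.** Amend sections 2.4 and 2.10:

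1. Name one confirmatory time point, for example T4, the end of treatment, and treat the other visits as supportive.
2. For the primary indicators, replace the blanket P < 0.05 rule with one procedure that holds an overall two-sided 0.05. The options are:
   - Holm across the four, with a first threshold of 0.05 / 4 = 0.0125;
   - a fixed sequence, each test at 0.05 and stopping at the first failure, in an order that the sponsor sets before unblinding;
   - a single primary indicator, with the other three secondary;
   - a requirement that all four be significant, each at 0.05.
3. Label all other P values nominal.

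The edit takes a few sentences. The price depends on the option. Holm raises the difference that the trial can detect at its first step (step 5 of the working). A fixed sequence splits no alpha, but a failure early in the order blocks everything after it. A single primary indicator narrows the confirmatory claim to that indicator. An all-four rule needs no adjustment but lowers power. The choice among them, and the order of any sequence, is the sponsor's.

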## 3. Discussion

Recently, many studies have used the Zhenyuan capsule as treatment for CHD, heart failure [11], and type 2 diabetes [12] with Qi deficiency or blood stasis. The benefits of the treatment are clear. In addition, the effect of the Zhenyuan capsule in the treatment of CHD with abnormal glucose and lipid metabolism has been observed in clinical settings, but the evidence is not strong. This study intends to examine the clinical efficacy and safety of the Zhenyuan capsule for treating these diseases in a randomized, double- blind, and parallel-controlled trial.

This study first applies the Zhenyuan capsule for blood lipid research. This may reveal new uses for old drugs in TCM. In addition, this is the first study to address the efficacy and safety of the Zhenyuan capsule for CHD with abnormal glucose and lipid metabolism in a double-blind and parallel-controlled trial. We assume that this design, which is in line with the TCM theory, will contribute to more convincing results and robust evidence for the efficacy of study medications.

This study has some limitations. Owing to the complexity of the disease, many potential influencing factors may exist. Therefore, to minimize possible errors, participants will have a 2-week run-in period. During this period, any TCM medications for improving blood lipids or glucose will not be permitted. In addition, participants will not be permitted to use other treatments for angina pectoris in CHD and diabetes mellitus, including TCM herbs and Chinese patent medicines at any time during the study.

In summary, by rigorous design, the results of this study will provide clinical evidence regarding the efficacy and safety of Zhenyuan capsules for CHD with abnormal glucose and lipid metabolism.

## Figures and Tables

**Figure 1 fig1:**
[figure not shown]
Study flowchart.

**Table 1 tab1:** Measurement items and time points for data collection.

	Screening	Treatment period			
	T0	Run-in period (T1)	Week 4 (T2)	Week 8 (T3)	Week 12 (T4)
*Basic medical history recording*					
Informed consent	×				
Inclusion/exclusion criteria		×			
Demographic data		×			
Medical and treatment history recording		×			
Complication and symptom recording		×			
Concomitant medication		×	×	×	×
Vital signs		×	×	×	×
*Efficacy observation*					
TG, FBG, 2hPBG, and HbA1c levels	×	×	×	×	×
TCM symptom indicators		×	×	×	×
Seattle Angina Questionnaire score		×	×	×	×
Coagulation indicator		×	×	×	×
P-selectin level		×	×	×	×
Angina pectoris scores and end-point event		×	×	×	×
ECG		×			×
UCG		×			×
*Safety assessment*					
Liver and renal function tests	×	×	×	×	×
Hemorrhage		×	×	×	×
Routine blood and urine tests		×			×
Routine stool and occult blood tests		×			×
*Other works*					
Randomization and allocation		×			
Drug distribution		×	×	×	
Medicine recycling and drug quantity statistics			×	×	×

## Abbreviations

ALT: Alanine transferase
BUN: Blood urine nitrogen
CHD: Coronary heart disease
COURAGE: The Clinical Outcomes Utilizing Revascularization and Aggressive Drug Evaluation
CR: Serum creatinine
CRF: Case report form
CTA: Computed tomographic angiography
ECG: Electrocardiography
FAS: Full analysis set
FBG: Fasting blood glucose
GFS: Ginseng fruit saponin
HbA1c: Glycosylated hemoglobin
LDL-C: Low-density lipoprotein cholesterol
NCEP: National Cholesterol Education Program
PPS: Per-protocol set
SAQ: Seattle Angina Questionnaire
TC: Total cholesterol
TCM: Traditional Chinese medicine
UCG: Ultrasonic cardiography
2hPBG: 2-hour postprandial blood glucose.
